### Analyses of primary and secondary outcomes

The primary outcome is 30-day acute readmission. We will use relative risks to compare the readmission rates in the two groups. Relative risk for other readmission time frames will also be calculated to improve comparisons with other studies.

Competing risk of death will be considered in our analyses, as it can skew the results. Partially due to this, days out of hospital will also be calculated as it is less affected by the competing risk of death than a binary readmission outcome.

We will also calculate the relative risks for 30-day mortality.

A proportional hazard model will be used to explain the time to readmission. This will be done using the Cox regression model. Moreover, median time to readmission will be estimated by the Kaplan–Meier method.

We will include relevant patient characteristics that are known risk factors in our statistical analyses, e.g. multimorbidity, polypharmacy and length of stay.

Throughout the analyses, we will adjust for participants that were already readmitted at the time of recruitment. Separate analyses will be done for patients that already received the intervention, as there may be a residual effect of the intervention.

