The Department of Geriatric Medicine at Odense University Hospital is a specialised medical department with geriatric specialist consultants caring for up to 32 in-hospital beds and a large outpatient clinic. In 2018, there were 2232 unique patients discharged from the ward. The mean age was 82.4 years, and the mean LOS was 6.1 days. The Department of Geriatric Medicine at Odense University Hospital receives acutely admitted geriatric patients, which are characterised by medical complexity, high age, multimorbidity, polypharmacy and functional loss. Medically non-complex patient with a simple single disorder (e.g. otherwise healthy adult with pneumonia) are allocated to any specialised internal medicine ward but may also be allocated to G-OUH according to availability of beds. However, due to the vast number of older medically complex patients, simple single disorder patients are few at G-OUH. The most common primary discharge diagnoses of patients discharged from G-OUH are acute infections and dehydration, but with considerable overlap with a variety of other common diagnoses, e.g. falls, rhabdomyolysis, heart failure, chronic obstructive pulmonary disease (COPD) and delirium.

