### Eligibility

A project coordinator identifies eligible patients among all patients admitted to G-OUH.

Only patients transferred to G-OUH ward are screened for eligibility, and thus patients discharged directly from the AMU are not included.

Criteria for eligibility are patients admitted to G-OUH and discharged to their own home and in need of personal care provided by the municipal home care organisation in Odense Municipality. Patients discharged to care home are also included. Exclusion criteria are patients discharged to other skilled nursing facilities or discharged with no need for personal care. Also, terminally ill patients and incapacitated patients, e.g., patients with moderate or severe dementia are not eligible. Patients with dementia are excluded if they are unable to live independently (i.e., if they require a care home or are completely dependent on their spouses to remain at home). In cases of uncertainty, a senior geriatric consultant will assess the cognitive function and determine severity. Patients that are delirious throughout the entire hospital stay will also be excluded, as they cannot give informed consent. Patients with active delirium are reassessed by a project manager based on indications such as confusion to orientation (to personal data, treatment, location, time and recent events), ability to concentrate and follow a conversation, organisation and coherence of thought, and overall mental status, as assessed by the CAM score. In cases of uncertainty, patients are not included. Finally, while initially excluding readmitted patients who had already been enrolled as study participants, it was decided after 4.5 months from the start of the study to allow the inclusion of readmitted study participants. The change was made due to an insufficient entry of eligible participants following a shortage of staff and a cut in the number of hospital beds at G-OUH. The original eligibility criteria were thus slightly changed to allow readmitted patients to participate. We decided to include these patients due to the uncertainty of future patient flow, knowing that we can adjust for this factor in the analyses after the trial.

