***Secondary outcomes***		
Outcome 3	Mortality (1 year)	Proportion of participants deceased within one year
Outcome 4 Outcome 5	Time to Readmission Days alive out of hospital	Proportional hazard model of readmission with a total duration of 1 year and median time to readmission estimated by Kaplan–Meier method Days spent alive out of the hospital within 30 and 90 days from discharge
Outcome 6	Clinical assessments/POCT measurements and their association to decision making	Regression analysis of the association between conducting a clinical measurement (e.g. Saturation, temperature, Sodium, CRP) or POCT analysis and the risk of readmission
Outcome 7	Costs associated with the intervention	Analysis of the costs associated with the intervention and potential savings from the result of the intervention
Outcome 8	User perspectives among involved participants and professionals	Analysis of questionnaires and focus group interviews with involved groups, including participants, community nurses, geriatric nurses, geriatric physician, and primary care physician

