### Data collection

Data will be collected at several points. The data will all be saved and stored in a secure database (REDCap). All personnel involved will be trained data collection.

Before the participant is invited to join the study, data is gathered on eligibility (i.e. diagnosed moderate to severe dementia, residence location to identify citizens of Odense Municipality, and type, use of home care, terminal diseases and presence of delirium).

Before discharge, data is gathered from the participants’ electronic medical records regarding discharge diagnoses, LOS, medication, medical history and Barthel ADL score [39]. A Clinical Frailty Score [40] is assessed by a geriatric nurse.

All data collected during the follow-up visit is registered in our database, including the data gathered in the FS-III survey, vital status and POCT results. The vital parameters and POCT results will be used to understand their influence on the clinical decision making.

The data collected during the follow-up visit will be filled directly into pre-defined fields in REDCap and will help ensure that all the necessary data is collected.

All participants, controls and interventions will receive a questionnaire, which is a modified version of a previously validated questionnaire [41]. At the time of randomisation, both groups will be asked about their satisfaction with the treatment, care and hospitalisation in general, as well as if they feel safe being discharged. A follow-up questionnaire will be administered to both groups by telephone. Data will be transferred to REDCap manually. The questionnaires will be administered by project coordinators who are not involved in the clinical care of the patients.

Data on death and readmissions will be collected from electronic medical records for 1 year after the allocation date for each participant.

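### The Kaplan–Meier median time to readmission over 1 year (Outcome 4) comes out too early if deaths are censored; a competing-risk curve should replace it

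*Protocol article*

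**What the plan says.** Two places in the protocol article fix the method for time to readmission. Table 2 defines Outcome 4 as: "Proportional hazard model of readmission with a total duration of 1 year and median time to readmission estimated by Kaplan–Meier method". The section on analyses of primary and secondary outcomes names Cox regression and repeats that "median time to readmission will be estimated by the Kaplan–Meier method". In both places the event is readmission, not readmission or death.

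The same analysis section also states: "Competing risk of death will be considered in our analyses, as it can skew the results". The concrete response given there is that "days out of hospital will also be calculated as it is less affected by the competing risk of death than a binary readmission outcome". Table 2 defines that outcome at 30 and 90 days.

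The Data collection section says: "Data on death and readmissions will be collected from electronic medical records for 1 year after the allocation date for each participant". One-year mortality is a secondary outcome in Table 2 ("Proportion of participants deceased within one year"), but no expected rate is given for it, nor for readmission at 1 year.

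**The concern.** A patient who dies at home in month three can no longer be readmitted. If that death is censored, Kaplan–Meier assumes that the patient's later readmission risk equals that of the survivors. Its complement then estimates readmission in a setting where nobody dies, which lies above the proportion actually readmitted. A curve that lies too high crosses 50% too soon, so the median is too early. If deaths differ between arms, the two medians are shifted by different amounts.

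The article recognises the threat and then, in the same section, names an estimator that does not deal with it. Days out of hospital is a separate outcome with a horizon of at most 90 days, so it cannot repair a 1-year median. This is a method stated twice, not a detail left open. An analysis plan that followed the text would carry the bias, and one that used another estimator would depart from the published method.

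**Working it through.** **Direction.** Let λr and λd be the cause-specific hazards of readmission and of death before readmission, and Λr and Λd their cumulative forms.

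- Kaplan–Meier with deaths censored estimates 1 − exp(−Λr(t)), which equals ∫ λr exp(−Λr) du.
- The proportion actually readmitted by time t is F(t) = ∫ λr exp(−Λr − Λd) du.

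Since exp(−Λd) ≤ 1, the first is never below the second, and it is strictly above once anyone at risk has died and readmissions continue. No rate needs to be assumed for this.

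**Inputs for the size.** The article has no figure of its own for this outcome to reproduce. The only usable one is the control readmission rate of 19% (sample size section), taken here as the 30-day value. The 1-year rates are assumptions: R, the proportion readmitted within 365 days (40–60%), and D, the proportion dying before any readmission (5–20%). The readmission hazard is λ1 up to day 30 and λ2 afterwards; the death hazard d is constant. The three hazards are solved so that F(30) = 0.19, F(365) = R and deaths first by day 365 = D.

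**Worked case, R = 50%, D = 15%.** The solution is λ1 = 0.007106, λ2 = 0.001711 and d = 0.000722 per day.

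- F(30) = (0.007106 / 0.007828) × (1 − exp(−0.007828 × 30)) = 0.190.
- Free of both events at day 30: exp(−0.007828 × 30) = 0.791.
- F(365) = 0.190 + 0.791 × (0.001711 / 0.002433) × (1 − exp(−0.002433 × 335)) = 0.50, so the median is day 365.
- Kaplan–Meier complement at day 365: 1 − exp(−(30 × 0.007106 + 335 × 0.001711)) = 0.545.
- Kaplan–Meier median: 30 + (ln 2 − 30 × 0.007106) / 0.001711 = 310.5, so day 311, which is 54 days early.

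**All scenarios** (first whole day on which the curve reaches 50%):

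| Readmitted in 1 year | Dying first | Kaplan–Meier at 1 year | Kaplan–Meier median | Cumulative-incidence median | Days early |
|---|---|---|---|---|---|
| 60% | 5% | 61.8% | 245 | 255 | 10 |
| 60% | 10% | 63.9% | 230 | 249 | 19 |
| 60% | 20% | 69.2% | 197 | 234 | 37 |
| 55% | 5% | 56.6% | 290 | 303 | 13 |
| 55% | 10% | 58.3% | 274 | 299 | 25 |
| 55% | 20% | 62.7% | 238 | 289 | 51 |
| 50% | 5% | 51.3% | 348 | 365 | 17 |
| 50% | 10% | 52.8% | 330 | 365 | 35 |
| 50% | 15% | 54.5% | 311 | 365 | 54 |
| 50% | 20% | 56.4% | 291 | 365 | 74 |
| 45% | 5–15% | 46.1–48.6% | not reached | not reached | – |
| 45% | 20% | 50.2% | 363 | not reached | – |
| 40% | 5–20% | 40.9–44.1% | not reached | not reached | – |

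**Short horizon.** In these scenarios the Kaplan–Meier complement at day 30 is 19.1–19.3% against 19.0%. At day 90 the excess is at most 1.2 percentage points (32.1% against 30.9%, at 60% and 20%). The problem belongs to the 1-year horizon.

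**The case against.** The strongest reply is that the article never says how deaths enter the Kaplan–Meier analysis, that it promises in general terms to consider competing risk, and that the choice of estimator may be left to an analysis plan not shown here. Part of this stands: censoring is the standard reading of a readmission-only event, not a written rule. If the dead were instead carried event-free to day 365, the curve would match the cumulative incidence under complete follow-up. But the general promise attaches no remedy to Outcome 4, while a specific estimator is named for it twice.

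The size is also open to challenge, and this stands too. The largest gaps occur when readmission is close to 50%, because the curve is shallow where it crosses the median. At 55–60% readmitted with 5–10% dying first, the gap is only about 10 to 25 days, and at 40% no median is reported by either method.

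A reader might infer more than the documents support:

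- **High mortality.** No rate is stated. For the ward's discharges in general, "The mean age was 82.4 years, and the mean LOS was 6.1 days"; the age makes deaths plausible but does not give a rate. The eligibility rules also remove some of the patients most likely to die: "Also, terminally ill patients and incapacitated patients, e.g., patients with moderate or severe dementia are not eligible".
- **Wrong readmission levels.** No Kaplan–Meier probability is a named output. Levels are to be compared as relative risks at fixed times, and with complete follow-up the crude proportion readmitted by a date already equals the cumulative incidence at that date.
- **A faulty treatment comparison.** The comparison in Outcome 4 is the Cox model, which with deaths censored is interpretable as a cause-specific hazard ratio. The primary 30-day relative risk does not use Kaplan–Meier.
- **A median that may not exist.** This is not an error in itself; it would be reported as not reached.

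**Conclusion.** The point holds for one secondary, descriptive statistic: the 1-year median time to readmission. Given that deaths are censored, the estimated median is too early whenever patients die before readmission and it is reached. That direction rests on no assumed rate.

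The size rests entirely on assumed 1-year rates and on the piecewise-constant hazards used above. It is about 10 to 75 days for 50–60% readmitted and 5–20% dying first. At 45% readmitted and 20% dying first, Kaplan–Meier reports day 363 although 55% of patients are not readmitted within the year. At 40% readmitted there is no median to be wrong. The documents do not support a conclusion that the primary result or the Cox comparison is compromised.

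**What to change.** In Table 2 (Outcome 4) and in the section on analyses of primary and secondary outcomes:

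1. Replace Kaplan–Meier by the Aalen–Johansen cumulative incidence of readmission, with death as the competing event, by arm over 1 year.
2. Read the median from that curve, and report it as not reached if the curve stays below 50%.
3. Keep the Cox model, label its result as the cause-specific hazard ratio for readmission, and report the cause-specific hazard ratio for death beside it.

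Any separate analysis plan should carry the same wording. The change needs no new data, since deaths and readmissions are already collected for 1 year, and the analysis is standard in the stated software. The downside is a slightly longer results table.

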## Discussion

The future will pose a major challenge by the increasing number of older adults with complex health issues and in need of acute hospital admission. The future also implies a shortage of health care professionals in both primary and secondary care and fewer hospital beds. Preventing acute admissions and readmissions where possible is central for the well-being of the older population as well as for health care providers. Even disregarding the future challenges, preventable readmissions are of no benefit to anyone. The process of readmitting is stressful for the municipal home-based-care system, and readmissions increase pressure on the hospitals and, most importantly, have a negative impact on the patients. Preventing readmissions would be a benefit to society as a whole. Therefore, it is highly important to understand which health problems arise after discharge, especially in the first week, which is where the majority of acute readmissions occur.

The reasons for acute readmission are multiple as well as complex and mixed, and some are even unavoidable. Certain risk factors have been identified, but current tools to predict readmission (e.g., ISAR, LACE) have not yet been proven effective and further research is needed [44, 45].

Several items in transitional care are important. A list of potential issues can include poor communication between the discharging ward and the home care district resulting in lack of important information regarding the needs of care for the patient, incomplete organisation and delivery of aids, insufficient knowledge by the discharging ward of the patient’s home environment, lack of competences by the home carers, inability to recognise early signs of worsening health and delayed contact with the primary care physician after discharge. We seek to understand the factors involved in the transition from hospital to home, to intervene upon some of them and to analyse the impact of our intervention.

Previous studies using follow-up visits have shown positive effects when carried out by a geriatric team consisting of a physician and a nurse or allied health professional [14, 15]. However, as personnel resources are scarce, we aim at a cross-sectoral intervention with a trained geriatric nurse, a systematic assessment of functions (FSIII), POCT equipment for rapid clinical assessment, real-time video consultation with a geriatrician from the discharging hospital ward, and, not the least, a cross-sectoral face-to-face communication with the municipal care providers, the participants and possible relatives. This is a novel approach that, to our knowledge, has not previously been investigated. The intervention is multifactorial. As such, we will not be able to disentangle whether it is the coordinated home visit alone, the systematic approach, the clinical in-home assessment or the video consultation that is the most important. The present study is a pragmatic trial, based on the principles of Clinical Geriatric Assessment (CGA), with a holistic and cross-sectoral approach.

This study has several strengths and weaknesses. In terms of strengths, the study is a major RCT and thus it will yield a high level of evidence. The coordinator, who randomises the participants, will have no influence on treatment and care of the participants and thus no effect on readmission. The randomisation will be carried out at discharge, not during the admission, which ensures that the hospital staff is blinded and thus unbiased. As it is an RCT study, the survivorship bias will be low.

An additional strength of this study is that we also analyse the health economic aspects of the intervention, which is expected to be an important factor for potential adoption of this intervention in other clinical settings treating care needing older adults, e.g., orthopaedic departments discharging hip fracture patients. Equally important is the qualitative data from the user’s perspective.

In terms of weaknesses, there will be a selection bias towards cognitively intact or mildly cognitively impaired patients with, at most, a diagnosis of mild dementia, as patients with moderate to severe dementia will be excluded due to the current research-ethical constraints regarding the inclusion of incapacitated patients. Yet, we believe that patients with moderate to severe dementia would benefit from the intervention, too. There may also be a performance bias, as participants in the intervention group may withhold contact to primary care physician if they feel worse after discharge as they know they will receive a follow-up visit shortly. The same performance bias is expected among the home care staff who visits the participants. This type of bias may lead to lower readmissions on its own.

Finally, the intervention is multifactorial encompassing multiple elements: (a) a home visit soon after discharge that may reassure both the participant, the relatives and the home care so that contact to the primary care physician is prevented, (b) a systematic approach securing that all potential bodily functions are assessed, (c) the use of vital status assessment and POCT analyses and (d) video contact to a geriatrician from the discharging department. We will thus not be able to disentangle, which of the elements has the greatest effect in the intervention, but as geriatric patients are complex, all elements of the interventions may add valuable information that supports clinical decision-making and relevant care to the patient.

### Trial status

The study has begun on November 1st, 2022. The original date was postponed due to a severe nursing staff shortage in Denmark in the aftermath of COVID. We achieved the necessary funding and approvals to begin the study and have begun trial. The first month (November 2022) of the trial was conducted as a pilot and the data will not be included in the final data set. Difficulties include hospital policy changes that has resulted in fewer patients allocated to our ward, and a larger than expected proportion of patients that are not from the Odense Municipality. Due to these challenges, we now include readmitted patients as described earlier, as this can be adjusted in data analysis.

Protocol Version 1. Date: April 15th, 2024

Name and contact information of the trial sponsor:

[name], Professor, PhD

Department of Geriatric Medicine, Odense University Hospital, Odense, Denmark

[name]

[name]

Denmark.

Email: [contact].

Phone: [name]

Role of sponsor: Not applicable

## Data Availability

Data sharing is not applicable currently. Whether data sharing will be possible after finishing the study in the future relies on obtaining permission from the Danish Data Protection Agency.

## Abbreviations

LOS: Length of stay
G-OUH: Department of Geriatrics, Odense University Hospital
POCT: Point-of-care-testing
OUH: Odense University Hospital
COPD: Chronic obstructive pulmonary disease
AMU: Acute medical unit
FS-III: Fælles Sprog III (English: Common Language III)
OPEN: Open Patient data Explorative Network
RNG: Random Number Generator
CGA: Clinical Geriatric Assessment
ADL: Activities of Daily Living
SPIRIT: Standard Protocol Items: Recommendations for Interventional Clinical Trials
CONSORT: Consolidated Standards of Reporting Trials
